### Criteria for stopping treatment

2.11

Participants could stop the treatment and drop out of the research project for any reason at any time, and the reason for the drop out will be recorded in their CRF. The participants will be told that they have the right to drop out of the experiment and that they will be provided the standardized treatment if they drop out. The criteria for stopping treatment and dropping out from the research project are:

The participant has suffered from a serious medical disease, and could not receive surgical treatment or rehabilitation exercise according to the plan.The participant could not have a regular follow-up or cooperate with telephone follow-up.Poor compliance, such as unable to have a regular follow-up or cooperate with telephone follow-up.In addition to the standardized treatment of the Department, a whole set of exercise plans of other rehabilitation physicians were implemented.

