**Discussion::**

Exercise under monitor may improve patients compliance and exercise quality, and accelerate the rehabilitation process. This protocol reported in accordance with the CONSORT 2010 checklist and SPIRIT 2013 Checklist.

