### Study design and setting

2.1

This is an opening, prospective, double-dummy RCT. There are 50 patients in total with femoral neck fracture will be recruited from the First Affiliated Hospital of Guangzhou University of TCM, Guangzhou, China. The flow chart and study period are shown respectively in Figure 1. After obtaining written informed consent, the eligible participants will get complete examination before surgery as well as hemiarthroplasty, and then they will be randomly assigned to a monitoring group or a control group in a 1:1 ratio.

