#### The control group

2.6.1

The patients of this group of the control group will carry out the staged rehabilitation exercises according to the definite exercise plans, and record the daily exercise in Figure 3 and give it to the doctors during the follow-up. The doctor in charge needs to repeatedly preach and teach during hospitalization to ensure that patients and their families understand the importance of postoperative rehabilitation exercise, and give family exercise guidance after 2 weeks (the same as the experimental group). Regular outpatient follow-up after discharge. If patients have any questions about the rehabilitation process, they should call for a consultation, and do not take the initiative to call for follow-up. Two weeks, 1 month, 3 months, and 6 months after the operation, an outpatient face-to-face examination will be carried out.

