#### The secondary outcome

2.7.2

The Secondary outcome measures are as follows:

Activity of Daily Living (ADL): it refers to the necessary activities that a person carries out every day to meet the needs of daily life, including eating, dressing, washing, bathing, toileting, dressing, etc. Functional movement includes turning over, sitting up from bed, transferring, walking, driving a wheelchair, going up and downstairs, etc. The total score is 100 (100 points: life self-care; 60 points and above: basic self-care; 40 to 60 points: life needs assistance; 20 to 40 points: life needs great assistance; less than 20 points: life completely dependence.)The timed “up & go” text: a fast and quantitative evaluation method of functional walking ability only needs a chair and a stopwatch. During the assessment, the patient is sitting on the chair with the back of the chair and hands on the armrest. If the walking aid is helpful, the walking aid is held in the hand. The reference object set 3 meters away from the seat. With the tester sends out the command of “start”, the patient stands up and walks to the reference point and returns. There is none physical help during the test. The tester records the time taken (in seconds) and the risk of falling during the completion of the test. Before the formal test, the patient is allowed to practice 1 to 2 times to ensure that the patient understands the whole test process. Researchers need to record the complete time of the experiment and evaluate the risk of completing the action. (1 point: normal. 2 points: very slight abnormality. 3 points: slight abnormality. 4 points: moderate abnormality. 5 points: severe abnormality.)Visual analog scale (VAS): The subjects participating in the study will indicate the intensity of their pain using a VAS of 100 mm. They must signal on a horizontal line of 100 mm where they would place their pain, where 0 mm indicated “no pain” and 100 mm would be “the worst pain imaginable”.Postoperative complications: Such as pulmonary embolism, lower extremity deep vein thrombosis, loosening, and displacement of the prosthesis, periprosthetic fracture, postoperative infection, etc.6-month mortality after HA:

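### Section 2.11 makes the treatment-stopping criteria also criteria for leaving the study, so randomised patients can lose follow-up for reasons that may differ between arms

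*Protocol article*

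**What the plan says.** Section 2.11 first allows any participant to leave at any time for any reason. It then adds a separate list, introduced with "The criteria for stopping treatment and dropping out from the research project are". One set of conditions therefore governs two different things: the end of the intervention and the end of participation. The list contains:

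- illness: "The participant has suffered from a serious medical disease, and could not receive surgical treatment or rehabilitation exercise according to the plan";
- failure to attend follow-up or to cooperate with it by telephone;
- compliance: "Poor compliance, such as unable to have a regular follow-up or cooperate with telephone follow-up";
- outside rehabilitation, where "a whole set of exercise plans of other rehabilitation physicians were implemented".

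For patients who leave, the section provides that the reason goes into the CRF and that standardised treatment is offered. It does not say that they continue to be assessed.

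On timing, section 2.1 places consent, examination and hemiarthroplasty first, "and then they will be randomly assigned to a monitoring group or a control group in a 1:1 ratio". On outcomes, section 2.7 measures HHS at weeks 2, 4, 12 and 24, and section 2.7.2 lists complications and "6-month mortality after HA" as secondary outcomes. Section 2.5 states that the trial is open.

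**The concern.** A randomised comparison is protected only while the patients who were randomised go on being measured. Here a patient can stop being measured because of something that happens after allocation: falling seriously ill, taking up other rehabilitation, or being judged poorly compliant. In an open trial of a monitoring and reminder system, each of these may occur at a different rate, or in a different kind of patient, in the two arms. Those who remain to week 24 may then no longer be comparable.

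The prescribed programme lasts 2 weeks and follow-up lasts 24. After week 2 the list therefore acts mostly as a rule for ending follow-up. Section 2.9 sizes the trial on HHS at 6 months, which is the assessment most exposed.

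The illness criterion also bears on the safety outcomes. Patients who become seriously ill are those in whom later complications or death are most likely, and once they have left the project nothing in the text secures that later information.

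**Working it through.** **Step 1. Which criteria act after randomisation.** Surgery precedes allocation (section 2.1), so inability to receive surgery acts before it. Serious illness preventing exercise, missed follow-up, poor compliance and outside rehabilitation can all act afterwards.

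**Step 2. The telephone criterion.** Section 2.11 counts failure to cooperate with telephone follow-up as a ground for leaving. For controls, section 2.6.1 says that if they have questions "they should call for a consultation, and do not take the initiative to call for follow-up", which reads as no calls initiated by the study team. Sections 2.6.1 and 2.6.2 schedule face-to-face outpatient visits. It is unclear what telephone follow-up a control could fail to cooperate with.

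**Step 3. The plan's own figure (section 2.9).** Difference 92.650 − 86.580 = 6.07. Pooled SD = √((4.629² + 3.664²)/2) = 4.174. For a one-sided 5% test with 90% power, n = 2 × (4.174 × (1.645 + 1.282)/6.07)² = 8.10 per group. Dividing by 0.8 for 20% loss gives 10.1, so 11, which matches the stated number (rounding 8.10 up to 9 first gives 12). The 20% loss is one overall figure, not split by arm or by reason.

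**Step 4. Illustration of the bias.** Let a share q of an arm leave, and let leavers score D points below those who stay. The mean of those who stay exceeds the mean of all randomised by q × D. With the same D in both arms,

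bias (monitoring − control) = (q_mon − q_con) × D.

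The values of q and D are assumptions. D is set at one pooled SD (4.17), the planned difference (6.07) and a larger value (10). With no true effect, 25 randomised per arm and SD 4.174, SE = 4.174 × √(1/(25(1 − q_con)) + 1/(25(1 − q_mon))). The two-sided 5% test then rejects with probability Φ(−1.96 + b/SE) + Φ(−1.96 − b/SE), where b is the bias.

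| Leave: control / monitoring | Bias at D = 4.17 / 6.07 / 10 | Type I error |
|---|---|---|
| 20% / 20% | 0 / 0 / 0 | 5% throughout |
| 20% / 10% | −0.42 / −0.61 / −1.0 | 6.2% / 7.6% / 12.2% |
| 10% / 20% | +0.42 / +0.61 / +1.0 | 6.2% / 7.6% / 12.2% |
| 30% / 10% | −0.83 / −1.21 / −2.0 | 9.6% / 14.9% / 32.4% |

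Equal rates are not enough if different patients leave. With 20% leaving each arm, D = 6.07 in one and 4.17 in the other, the bias is 0.20 × 6.07 − 0.20 × 4.17 = 0.38 points.

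**Step 5. Whether the sample can carry the fix.** Suppose 20% of monitored patients stay in follow-up but gain nothing. The effect becomes 6.07 × 0.8 = 4.86. Two-sided power is Φ(4.86/(4.174 × √(2/n)) − 1.96), which is 98.4% with 25 per group and 95.7% with 20. If 30% gain nothing, the effect is 4.25 and power is 94.9% and 89.6%.

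**The case against.** Several stronger readings are tempting, and the text does not support them.

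**That patients are removed for not exercising, the very behaviour the device targets.** The abstract does say "Exercise under monitor may improve patients compliance and exercise quality". But the only examples section 2.11 gives of poor compliance are missed clinic or telephone follow-up, and no criterion names missed exercise in an otherwise well patient. The term is open-ended and, read narrowly, largely repeats the criterion before it, so a wider use is possible but not stated. Patients who cannot be reached would mostly lack outcome data anyway. The rule matters most for the seriously ill and for users of other rehabilitation, who may still be measurable.

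**That more controls leave, so the bias runs against the device.** If reminders keep patients in the trial, that would follow. But section 2.6.2 has the device log exercises automatically against a set standard, while controls keep their own record (section 2.6.1). If exercise compliance were policed, failures would be easier to see in the monitored arm, and removing those patients would favour the device.

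**That the bias can be estimated.** Treating removal as truncation on exercise compliance, the mean shift is ρ × SD × φ(z)/(1 − p), where p is the share removed and z the matching normal quantile. With ρ from 0.3 to 0.5, removal of 20% versus 5% gives a net 0.37–0.61 points, and 40% versus 10% gives 0.68–1.13. The arithmetic is right, but every input except the SDs is assumed, the mechanism is not in the text, and the second scenario averages 25% loss against the planned 20%.

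**That complications and deaths are lost.** Death is not a removal criterion. A complication that triggers removal has already happened, and the reason goes into the CRF. Only later events and later vital status are at risk.

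It is also fair to say that the article does not exclude data already collected, and that an analysis plan not shown may define the analysis set. Its absence here is no fault. That does not answer the main point, because no analysis plan can recover assessments that were never made.

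**Conclusion.** The concern holds in a limited form. As written, section 2.11 ends participation, not only treatment, for randomised patients who meet any of its criteria, and nothing shown keeps them in follow-up. The 24-week HHS comparison may be biased in either direction, and later complications and 6-month vital status of the sickest patients may be missed.

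No size can be derived from the document. Under the assumptions in the working, with equal score deficits in both arms, the bias is zero when equal shares leave, 0.42 to 1.0 points at 20% versus 10%, and 0.83 to 2.0 points at 30% versus 10%. That is modest to moderate against 6.07. For complications and mortality, one patient is 1/25 = 4% of an arm; this shows how coarse the counts are and does not estimate the undercount. The case for change rests on keeping the randomised comparison intact, not on a particular number.

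**What to change.** Split section 2.11 in two.

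1. **Stopping treatment.** Leave the clinical criteria to the clinicians; nothing here bears on their content.
2. **Leaving follow-up.** State that meeting a treatment-stopping criterion, poor compliance or outside rehabilitation does not end follow-up, and that only withdrawal of consent to data collection does.

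Keep all randomised patients on the week 2, 4, 12 and 24 assessments, obtain 6-month vital status, and compare patients in the group to which they were assigned. Record compliance and outside rehabilitation as data. Reconcile the telephone criterion with section 2.6.1.

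The cost is wording, plus a small effort to see patients who have stopped treatment at visits that are already scheduled. The measured effect may be somewhat diluted, but under the plan's own difference and SDs the 50 patients can absorb that without a larger sample.

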### Ethical approval

2.12

The study protocol was approved by the Ethics Committee of the First Affiliated Hospital of Guangzhou University of Traditional Chinese Medicine (NO. ZYYECK [2020] 009), and registered in http://www.chictr.org.cn (ChiCTR2000033213). The study will be explicitly explained to all participants that the experiment involves 2 types of interventions, 2 weeks treatment and 24 weeks follow-up. Be hospitalized to HA is run-in period. All participants will be given sufficient time to decide whether to sign the informed consent form. Written informed consent must be obtained from each participant before they are randomized to a group. If there is any change in the research plan, the study will be suspended and a change application will be submitted to the ethics committee.

## Discussion

3

Because of the high mortality and disability rate of hip fracture,^[3]^ an increasing number of orthopedic surgeons have realized the importance of available rehabilitation plan of hip fracture after an operation. Compared with internal fixation, HA means earlier loads,^[5]^ it is safer to observe the movement of patients after HA. Although recommend rehabilitation within 48 hours after hip fracture surgery has been widely acknowledged, the current guidelines were unable to answer the following questions: what kinds of exercises are most suitable? How much exercise will be appropriate? And if the patients could accept the prescribed exercise? At present, the published clinical research on rehabilitation exercise after HA, the descriptions of exercise completion quality are less, only a few articles mention about using of load monitoring equipment to measure the weight-bearing strength of the affected limb. In practice, to help patients recover better after HA, orthopedic surgeons can only formulate a Home-Based rehabilitation scheme and use various means to increase the number of follow-up visits and to urge patients to carry out rehabilitation exercises,^[26–29]^ which would burden health care system. The main function of the equipment used in the study is to monitor the completion of the exercise and remind when the exercise is not completed. At the same time, the user's joint movement angle, lower limb weight-bearing force, stride, muscle contraction force, and other contents can be recorded, which provides the basis for our next research.

As far as we know, this is the first clinical study of hip fracture, which is focused on the interaction between early rehabilitation exercise quality and hip function. We designed this opening, double-dummy RCT system, try to obtain a better understanding of the status of rehabilitation exercises for postoperative patients, and observe the relationship between the quality of exercise completion and functional recovery after HA.

## Limitation

4

In this study, there are also some limitations. First, our study needs the active cooperation of researchers, so it is difficult for us to design a double-blind experiment. Second although the sample size is estimated, monitoring equipment used in our study involving motion monitoring, big data analysis, and communication based on Intern et between doctors and patients, which is an important innovation and quite different from the previous motion monitoring equipment, maybe in the future we have to recalculate the sample size according to the pre experiment results. Third, the current conditions make it difficult to carry out multi center and multi region research. Looking forward the cooperating with more institutions to expand the sample size after the completion of our single center research.
